### Landmark method

The ipsilateral anterosuperior region of the chest is shaved if necessary and skin disinfected with 2% chlorhexidine. If necessary, a local anesthetic (1% lidocaine solution) is applied. The needle is inserted 1 cm inferior and 1 cm lateral to the junction of the middle and medial thirds of the clavicle. Patients for whom cannulation is not possible with the landmark method will undergo the procedure under ultrasound guidance on the ipsilateral side. If highlighted thrombosis occurs, the patient will be withdrawn from the study and will undergo the procedure under ultrasound guidance on the contralateral side.

Correct placement of the tip of the catheter after the procedure is defined as <2.9 cm caudal to the right tracheobronchial angle to avoid intracardiac placement, as previously described
[10].

### Ultrasound method

The area is prepared (skin disinfection with 2% chlorhexidine, local anesthesia with lidocaine 1%) and draped sterilely as described above. In addition, the ipsilateral internal jugular and contralateral subclavian areas are prepared in case of catheter misplacements for proper ultrasound-guided repositioning. An Envisor or CX-50 ultrasound machine (Philips, Andover, MA, USA) equipped with a high-resolution 7.5-MHz transducer is used. The transducer is covered with ultrasonic gel and wrapped in an intraoperative sterile sheath (CIV-Flex^TM^ Transducer cover, 14 × 147 cm; CIVCO, Kalona, IA, USA).

The ultrasound method applied for SCV catheterization is a four-step procedure:

1. Preprocedural ultrasound scanning, through an infraclavicular views, is performed to measure the depth and caliber of the subclavian vein and to evaluate its patency. Furthermore, it is used to identify adjacent structures. The infraclavicular approach is also chosen for the area of puncture; if this approach makes evaluation difficult, the supraclavicular approach will be considered
[11].

2. An infraclavicular approaches, as described previously
[7,12-14], is utilized to compare the ultrasound and landmark methods. Although we use a high-frequency transducer, which applies tissue harmonic imaging, depicting two-dimensional views of the vein is difficult. Physicians use sonoanatomic landmarks such as the acoustic shadows of the underlying first thoracic rib and of the sternum to select an area of interest. The needle is inserted at the midclavicular line or more laterally, 1 to 3 cm under the clavicle. Under ultrasound guidance, the needle is advanced through the area between the clavicle anteriorly and the first rib posteriorly. The transducer is maneuvered to depict the subclavian vein, either the longitudinal (in-plane) or the transverse (out-of-plane) axis, and to achieve an optimum plane of catheterization (Figures 
2 and
3). Doppler techniques are also used to confirm the two-dimensional findings.

**Figure 2 F2:**
[figure not shown]
**Out-of-plane view (short axis) of the needle entering the subclavian vein with the acoustic shadow in an infraclavicular approach.** N, needle; SCA, subclavian artery; SCV, subclavian vein.

**Figure 3 F3:**
[figure not shown]
**In-plane view (long axis) of guidewire placement in the subclavian vein using an infraclavicular approach.** AV, axillary vein; GW, guidewire; Rib 1, acoustic shadow on the first rib; SCV, subclavian vein.

3. The needle is advanced slowly, so that its trajectory and/or tip can be detected superficially, toward the lumen of the vein on the longitudinal axis, while being purposefully directed toward the acoustic shadow of the thoracic rib underneath, thus minimizing the risk of damaging the pleurae and lung if transfixion of the vein is inevitable. Therefore, the needle enters the lumen of the vessel at the level of the subclavian vein, depending on the angle of penetration and the depth of the vein from the skin surface. In addition, the course of the needle is dependent on adjustments performed by the operator to visualize its trajectory on the longitudinal axis. Hence, the angle of penetration and the course of the needle can be modified in each patient during catheterization, making this technique largely operator-dependent. If a supraclavicular approach is used, the needle is inserted with the probe placed in the supraclavicular fossa, just lateral to the clavicular head of the sternocleidomastoid muscle in a long or short axis. The needle enters the subclavian vein before its confluence with the internal jugular vein. 4) The guidewire is advanced according to Seldinger’s technique; thereafter, the internal jugular veins and the contralateral subclavian vein are scanned to identify possible misplacements, allowing the catheter to be repositioned under ultrasound guidance.

Postprocedural ultrasound examination includes detection of:

1. Pneumothorax, as determined from lung-sliding, comet-tail artifacts, lung-point and lung pulse. Between two ribs (identifiable by their acoustic shadow), the interface between the thoracic wall and the lung consists of a hyperechogenic line that represents both the visceral and parietal pleura. Lung-sliding is a to-and-fro movement of this hyperechogenic line, which follows respiratory movements
[15]. Comet-tail artifacts are grossly vertical artifacts spreading from the hyperechogenic line to the inferior edge of the screen
[16]. The lung pulse refers to the subtle rhythmic movement of the visceral upon the parietal pleura with cardiac oscillations

### Study endpoints

The primary endpoint is the procedure time between the beginning of the procedure (T0) and when the catheter is controlled (T4).

The secondary outcomes are the procedure times (T0 to T5) of the two strategies, rates of per procedure complications (pneumothorax, hemothorax, and misplacement), failure of the technique and central venous catheter infection (catheter-related sepsis without bacteremia or catheter-related bloodstream infections). Catheter-related sepsis without bacteremia and catheter-related bloodstream infections are described below:

1. Catheter-related sepsis without bacteremia is defined according to the combination of 1) fever (body temperature ≥38.5°C) or hypothermia (body temperature ≤36.5°C), 2) catheter colonization, 3) regression of fever or hypothermia within the 48 h following catheter removal and with no change in antimicrobial therapy, or presence of pus at the catheter insertion site, and 4) no other identified sources of infection.

2. Catheter-related bloodstream infections are defined as the combination of 1) fever (body temperature ≥38.5°C) or hypothermia (body temperature ≤36.5°C), 2) one or more positive peripheral blood cultures drawn 48 h before or after catheter withdrawal, 3) isolation of the same organism (same species and same susceptibility pattern) from the colonized catheter or from the catheter insertion site, or a blood-culture differential time-to-positivity of 2 h or longer, and 4) no apparent source of bacteremia other than the catheter. In patients with positive coagulase negative staphylococci bacteremia, at least two positive cultures from separate blood samples are required.

### Follow-up

The following variables are collected:

Pre-randomization and during baseline assessment - gender, age height, weight, cardiac status (hypertension, cardiac failure, and ischemic heart failure), respiratory status (history of chronic obstructive pulmonary disease, asthma status, and long-term home oxygen), smoking status, alcohol status, history of diabetes mellitus, IGS 2, SOFA, indication for the SCV catheter and blood parameters (WBC count, hemoglobin, prothrombin time, fibrinogen, urea, and creatinine).

During the catheter procedure - highlighted thrombosis, the various procedure times (T0 to T5), number of punctures, number of catheter kits used, change in cardiac rhythm during wire insertion, use of the supra- or infra-clavicular approach, out-of-plane or in-plane ultrasound approach, depth of the subclavian vein, difficulty of subclavian vein visualization (very easy, easy, intermediate, difficult, or impossible), switch of the puncture site, operator or randomization group, arterial puncture, absence of internal jugular or contralateral subclavian placement, control of contrast test, absence of pneumothorax, and hemothorax.

After the procedure - duration of catheterization, occurrence of catheter infection.

### Sample size estimation, protocol drop-out and suspension

Studies have shown that ultrasound can detect the absence of complications and the correct positioning of the catheter and can reduce the processing time of the audit report on chest radiographs
[8,22]. The standard deviation of the processing time varies between 5 min and 25 min. In this study, 2 × 133 patients are needed to detect a 10 min (standard deviation equals 25 min) difference in the primary outcome, at a two-sided α level of 0.05 and a statistical power of 90%. It was estimated that 10% of patients would cross-over or drop-out, resulting in a total of 300 patients, 150 in each group. An interim analysis is planned after enrollment of the first 82 (1/4 of inclusions) patients to review data relating to patient safety and quality of trial conduct (software East (Cambridge, MA, USA, http://www.cytel.com), Kim-DeMets method with Pocock boundary). The committee monitoring data and safety will recommend stopping the trial if its continuation will compromise patient safety, defined as a between-group difference in serious adverse events.

If ultrasound highlights a thrombosis, the other subclavian vein will be used for cannulation. If cannulation of the subclavian vein is impossible, the patient will be excluded from the study and cannulation will be attempted using the internal jugular or femoral vein. These patients will be analyzed according to their originally assigned group on an intention-to-treat (ITT) basis.

### Statistical analysis

Statistical analyses will be performed on ITT populations. Student’s unpaired *t*-test or the Mann-Whitney test (if appropriate) will be used for primary outcome analysis. The Shapiro-Wilk test will be used to assess normality, and the Fisher-Snedecor test to assess homoscedasticity. Analysis will be adjusted by random effects linear regression to 1) take into account adjustments for possibly confounding covariates selected according to clinical relevance (for example, history of venous central catheter procedures, failure rate of the technique) and 2) consider variations within and between centers and operators. All effect sizes will be reported with 95% confidence intervals. Other continuous variables will be analyzed identically. Categorical parameters will be compared in the randomized groups using unadjusted chi-square or Fisher’s exact test. Analyses will be adjusted using the previously described adjustment variables in a logistic regression model. If the frequency of missing data is >5%, an additional analysis will be performed using the multiple imputation method (software Stata command
[23]). All analyses will be performed using Stata statistical software, release 12 (StataCorp, College Station, TX, USA).

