**Methods/Design:**

The Subclavian Central Venous Catheters Guidance and Examination by UltraSound (SUBGEUS) study is an investigator-initiated single center, randomized, controlled two-arm trial. Three hundred patients undergoing SCV catheter placement will be randomized to ultrasound real-time guidance and examination or landmark guidance and radiographic examination. The primary outcome is the time between the beginning of the procedure and control of the catheter. Secondary outcomes include the times required for the six components of the total procedure, the occurrence of complications (pneumothorax, hemothorax, or misplacement), failure of the technique and occurrence of central venous catheter infections.

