## Background

Central venous catheters play an important role in patient care, especially in the intensive care unit (ICU). However, their use is associated with various complications, which occur more frequently when catheters are placed through routes involving the subclavian vein than through routes involving the internal jugular and femoral veins
[1,2]. Nevertheless, the subclavian vein route is associated with lower rates of infection and thrombosis and remains the route of choice in the ICU
[3,4]. Real-time ultrasound-guided central venous cannulation results in a lower technical failure rate (overall and on first attempt), faster access, and a reduction in mechanical complications, although this has been validated mainly for the internal jugular vein
[5,6]. One study reported that complications and failure rates of subclavian central venous (SCV) catheterization were lower for real-time ultrasound-assisted vein location
[7]. However, the only temporal parameter recorded was the time between penetration of the skin and aspiration of venous blood into the syringe; thus, the time required for the entire procedure has never been evaluated. Ultrasonic diagnosis of catheter misplacement and pneumothorax related to central venous catheterization was reported to be a rapid and accurate method that can be easily performed by ICU physicians
[8].

The Subclavian Central Venous Catheters Guidance and Examination by UltraSound (SUBGEUS) study aims to compare the complete time required for the procedure and the rate of complications of a global ultrasound method and a standard (landmark and radiographic) method used in the routine cannulation of the subclavian vein in patients requiring a central line.

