## Methods/Design

### Objectives and design

The SUBGEUS study is an investigator-initiated, single center, randomized, controlled trial approved by the Institutional Review Board of Clermont-Ferrand, France (AU-1000, Eudra-CT 2012-A01188-35). Informed consent is obtained from each participant. The SUBGEUS study is conducted in accordance with the Declaration of Helsinki and was registered on June 25, 2013, on http://clinicaltrials.gov/ as trial NCT01888094.

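### The plan's example covariates for the adjusted models include failure of the technique, a secondary outcome that arises after randomisation, so the adjusted estimates would not be the total effect of assignment

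*Protocol article*

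**What the plan says.** The Statistical analysis section names a t-test or Mann-Whitney test for the primary outcome. It then describes a random effects linear regression that adjusts for "possibly confounding covariates selected according to clinical relevance (for example, history of venous central catheter procedures, failure rate of the technique". For categorical outcomes it names unadjusted chi-square or Fisher tests and adds: "Analyses will be adjusted using the previously described adjustment variables in a logistic regression model". No exception is made for any outcome.

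Failure is itself an outcome. Study endpoints lists "failure of the technique and central venous catheter infection" among the secondary outcomes, and the abstract does the same ("failure of the technique and occurrence of central venous catheter infections").

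The regression is also meant to "consider variations within and between centers and operators", although Objectives and design describes an "investigator-initiated, single center, randomized, controlled trial".

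**The concern.** Randomisation removes confounding by anything that precedes it. Failure of the technique does not precede it: it occurs during the procedure and may depend on the arm. It is a candidate mediator, not a confounder. Holding it fixed takes out whatever part of the time difference runs through failure. Patient difficulty plausibly affects both failure and time, so conditioning on failure can also introduce bias through difficulty.

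The adjusted estimate would be reported with a confidence interval beside the intention-to-treat comparison. The two could differ for reasons unrelated to chance baseline imbalance, and a reader could take the adjusted one as the better estimate. For the failure outcome, the adjusted model as written is circular.

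**Working it through.** **1. Is failure on the path from assignment to time?**
- Assignment to failure: Background reports one study in which "complications and failure rates of subclavian central venous (SCV) catheterization were lower for real-time ultrasound-assisted vein location".
- Failure to time: under Landmark method, "Patients for whom cannulation is not possible with the landmark method will undergo the procedure under ultrasound guidance on the ipsilateral side". Study protocol also resets T2 to the new puncture when the guide is not correctly inserted.
- The primary endpoint runs from T0 to T4, so this extra time is counted in it.

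The document itself supports both links.

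**2. The plan's own figure.** Inputs from the sample size section: difference 10 min, SD 25 min, two-sided alpha 0.05, power 90%.
- Normal approximation: n = 2 × (1.960 + 1.282)² × 25² / 10² ≈ 131.4, so 132 per group.
- t-test version: 132.3, so 133 per group, as stated.
- 266 / 0.90 = 295.6, so 296, consistent with 300.
- Power at 133 per group for 10 min (normal approximation): 90.4%.

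These figures stand; the covariate issue does not change them.

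**3. Size of the distortion.** The documents give neither failure rates nor minutes per failure, so both are assumed. If a failure adds m minutes in either arm and nothing else drives both failure and time:

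adjusted effect = total effect − (failure rate, landmark − failure rate, ultrasound) × m

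Total effect is set to the design value of 10 min.

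| Failure, landmark v ultrasound | m (min) | Removed (min) | Adjusted effect (min) | Power, 133 per group |
|---|---|---|---|---|
| 10% v 5% | 15 | 0.05 × 15 = 0.75 | 9.25 | 86% |
| 10% v 5% | 30 | 0.05 × 30 = 1.5 | 8.5 | 79% |
| 15% v 5% | 15 | 0.10 × 15 = 1.5 | 8.5 | 79% |
| 15% v 5% | 30 | 0.10 × 30 = 3.0 | 7.0 | 63% |
| 20% v 5% | 15 | 0.15 × 15 = 2.25 | 7.75 | 72% |
| 20% v 5% | 30 | 0.15 × 30 = 4.5 | 5.5 | 43% |

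The powers are rough. They keep the SD at 25 and ignore the residual variance that failure would explain.

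**4. Simulation check.** One large simulation assumed failure of about 14% v 5% and 20 extra minutes per failure.
- Time saved was 9.9 min unadjusted and 8.1 min with failure as a covariate.
- When patient difficulty also drove both failure and time, the figures were 10.0 and 7.6 min. Difficulty therefore added to the distortion under these assumptions.

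**5. The failure model taken literally.** A logistic model was fitted to 300 simulated patients with failure as the outcome and also as a covariate. It gave perfect separation and did not converge, and the standard error of the treatment term was above 20,000. No treatment effect can be estimated from such a model.

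**The case against.** **The phrase may mean an operator's past failure rate.** It says rate, stands next to a history item, and is followed by a term for variation between operators. On that reading it is a legitimate baseline variable and the circular model disappears. A reader might infer that this is ruled out because Follow-up lists no historical rate among the variables collected. That inference fails. The same list omits the paired example, catheter history, and has no item called failure of the technique either. What remains is that an operator rate is nowhere defined or listed as collected, while the wording matches a named outcome. The outcome reading is the natural one, not the only one.

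**The covariates are only examples, and an analysis plan not shown may fix the set.** This is true, and an analyst would probably drop failure from its own model. But the point is not an omission: the article offers an outcome as a suitable covariate.

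**The main tests are unadjusted.** This stands. A reader might infer that the primary comparison is compromised. It is not: none of the named unadjusted tests uses the covariate, and the document does not say that the adjusted model decides the conclusion.

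**The loss may be small.** A reader might infer that a large share of the benefit would be lost. For example, 20% v 5% with 40 extra minutes leaves 10 − 0.15 × 40 = 4 min. Nothing in the documents supports those inputs. The nearest figure, a 10% allowance for cross-over and drop-out together, is not a failure rate, but 20% v 5% averages 12.5% and exceeds it. At 10% v 5% with 15 minutes, the loss is 0.75 min, or 7.5%.

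**Conclusion.** The point holds for the adjusted analyses only. On the natural reading, adjusting for failure gives an estimate that is not the total effect of assignment. The direction depends on the trial's own failure rates: toward no effect if ultrasound lowers failure, as the one study cited in Background suggests, and in favour of ultrasound if it raises failure. The adjustment is wrong in both cases.

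The size cannot be derived from the documents. Under the assumed range above, the adjusted effect is about 9.25 to 5.5 min against a true 10 min, a loss of 7.5% to 45%. The lower end of that effect range rests on the most extreme assumptions. The sample size and the unadjusted comparisons are unaffected.

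The centre term is a minor wording slip. With one centre, a between-centre component cannot be estimated, but this biases nothing.

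**What to change.** - Delete failure of the technique, and any other variable that assignment can affect, from the covariates of every adjusted model, linear and logistic. Analyse failure only as an outcome.
- If an operator's past failure rate was meant, define it and state that it is fixed before randomisation.
- Restrict adjustment to named variables fixed before randomisation. The baseline list under Follow-up already offers candidates, for example body mass index from height and weight, prothrombin time and SOFA.
- Use history of central venous catheterisation, or the difficulty factors in Study protocol, only if recorded before allocation. That section describes the operator's difficulty assessment after randomisation. Short neck, agitation, acute respiratory failure and cannulation history are not in the baseline list.
- Keep operator as a random effect and drop the centre term.

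**Cost:** one or two sentences in the analysis section, and no new data if the covariates come from the existing baseline list. Any of the other factors would need confirmation that they were recorded before allocation. Because enrolment is under way, they may be missing for patients already included.

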### Data handling and record keeping

Data will be handled according to French law. All original records (including consent forms, CRFs and relevant correspondence) will be archived at the trial site for 15 years. The clean database file will be made anonymous and maintained for 15 years.

### Study organization

Financial support is provided by a research grant from the University Hospital of Clermont-Ferrand. The study is promoted by Clermont-Ferrand University Hospital.

The independent Data and Safety Monitoring Board (DSMB) ensures that the trial is in accordance with the Declaration of Helsinki, monitors patient safety and reviews safety issues as the study progresses. Serious adverse events and unexpected related or possibly related serious events are reported blinded to the DSMB within 24 hours and 7 days, respectively.

## Discussion

It has become clear that ultrasound approaches have potential applicability in central venous catheterization. All previous reports, however, have evaluated parts of the procedure time during real-time ultrasound guidance
[7]. The times of preparation of the transducer, which is covered with ultrasonic gel and wrapped in an intraoperative sterile sheath, and of the ultrasound guidance itself have not been yet evaluated. These may limit the findings showing that generalized ultrasound approaches reduce the time of catheter insertion. The SUBGEUS trial is the first randomized controlled study to investigate whether ultrasound real-time guidance and examination for SCV catheter procedure improves all procedure times.

The primary end-point of the trial is the total procedure time, from the beginning of procedure until the catheter is controlled. This time may be regarded as being more representative of the procedure time than the time between penetration of skin and aspiration of venous blood into the syringe.

The time to process audit reports on chest radiographs is reported to be very long, around 80 minutes, and may depend on the center. In contrast, the time required for ultrasound examination was much shorter (6.8 ± 3.5 min)
[8]. A prior evaluation in our institution showed that the median processing time was 20 min and ranged from 5 min to 25 min. The device used for chest radiography is located in our ICU, and the assistant radiologist must simply be called to take the radiograph with this device. Potentially, it may be difficult to generalize our results concerning this part of procedure.

Nevertheless, immediate ultrasound determination of the absence of misplacement or complications could allow the very early use of SCV catheters for multidrug perfusion in critically ill patients. The few minutes saved may represent a potential improvement of vital functions in the emergency room.

In conclusion, the SUBGEUS trial is an investigator-initiated pragmatic randomized controlled trial powered to test the hypothesis that a complete ultrasound approach (real-time guidance and examination) reduces the procedure time, from the beginning of the procedure to the end of checking the catheter. The SUBGEUS trial also determines the impact of the ultrasound approach on most procedure times and on the occurrence of complications.

